### Data Management

Baseline data will be collected using CRFs, which will include clinical observations, outcome measures, AEs, and safety evaluations. Outcome assessors, who are independent of the data management team, will ensure impartiality in evaluations, completing forms based on anonymous participant identifiers to maintain blinding. Completed CRFs will be entered into a Microsoft Excel database by 2 independent data administrators who are blinded to group allocations and trained in data monitoring. An independent data manager will oversee data entry into the International Traditional Medicine Clinical Trial Registry.

Data will be stored securely in both physical and digital formats, with access limited to the data manager. Upon trial completion, anonymization procedures will be implemented to preserve participant confidentiality, and an independent data analyst will perform statistical analysis on the anonymized data, ensuring objectivity and transparency.

### Quality Control

Rigorous quality control measures will be enforced by the steering committee. All researchers will undergo training in trial methodologies and monitoring techniques before participation. Any changes to the study protocol will be communicated to both the steering and ethics committees to ensure adherence to the original plan. The committees will also oversee recruitment, the intervention protocols (Tuina and acupuncture), and the quality of data collection.

### Statistical Analysis

All statistical analyses will be conducted using IBM SPSS 27.0 and R software (version 4.3.0), with a 2-sided *P* value of <*.05* considered statistically significant. Analyses will commence after the completion of follow-up for the last participant and will adhere to the intention-to-treat principle.

Changes in the primary outcome (VAS) and key secondary outcomes (WOMAC, 10MWT, pain threshold, and muscle tension) over time will be analyzed using linear mixed-effects models. These models will directly test whether the pattern of change from baseline through the 6-week and 18-week assessments differs between the Tuina and acupuncture groups (ie, a group×time interaction). If this interaction is significant, post hoc tests (ie, Bonferroni) will be conducted to identify the time points at which the groups differ.

The mixed-effects models appropriately handle missing data under the assumption that they are missing at random. A sensitivity analysis using multiple imputation will also be conducted to confirm the robustness of the primary results. Baseline characteristics will be summarized using means (SDs) or medians (IQRs). Differences between the 2 groups at baseline will be tested using *t* tests or Mann-Whitney *U* tests for continuous variables and chi-square tests for categorical variables. Correlations between changes in different outcomes will be assessed using Pearson or Spearman coefficients.

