### Sample Size Calculation

This study is designed as a superiority trial, with the sample size calculated using PASS 15 (NCSS, LLC). On the basis of relevant literature, a 2-point difference on the visual analog scale (VAS) score was defined as the superiority margin [36]. According to our preliminary experiments, the mean difference between the acupuncture group and the Tuina group (acupuncture-combined Tuina) is 3.25, with an SD of 1.5 in both groups. Using a superiority test with an *α* of .025 and a power of 0.8, and accounting for a 20% dropout rate, the calculated sample size is 30 cases per group, resulting in a total of 60 cases required.

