#### Primary Outcomes

The VAS score is based on a 10-cm long straight line, with the starting end marked as 0 points, indicating no pain, and the end marked as 10 points, indicating unbearable severe pain. Patients will select a point on the line that represents their current level of pain. A lower total score indicates reduced pain severity, reflecting the effectiveness of the interventions. This VAS is distinct from the VAS component within the short-form McGill Pain Questionnaire (SF-MPQ), which is used solely for screening purposes and for baseline characterization.

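### The trial is sized on one VAS difference against a 2-point margin, but the primary test is a three-visit group-by-time interaction with no named visit, contrast or margin

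*Protocol article*

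**What the plan says.** **Sample Size Calculation.** The trial is a superiority trial in which "a 2-point difference on the visual analog scale (VAS) score was defined as the superiority margin". From preliminary work, "the mean difference between the acupuncture group and the Tuina group (acupuncture-combined Tuina) is 3.25, with an SD of 1.5 in both groups". The remaining inputs are an alpha "of .025 and a power of 0.8, and accounting for a 20% dropout rate", and "the calculated sample size is 30 cases per group, resulting in a total of 60 cases required". The visit to which the 3.25 points refers is not given.

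**Primary Outcomes.** The outcome is a 0 to 10 VAS of present pain: "Patients will select a point on the line that represents their current level of pain". This section names no visit either. Table 1 schedules the VAS at screening, baseline, week 6 and week 18.

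**Statistical Analysis.** VAS and the key secondary outcomes go into linear mixed-effects models. The hypothesis tested is whether the two groups' courses over baseline, week 6 and week 18 differ, that is, the group-by-time interaction, at two-sided 0.05. Then: "If this interaction is significant, post hoc tests (ie, Bonferroni) will be conducted to identify the time points at which the groups differ". Baseline is one of the repeated visits. No baseline covariate and no common-baseline constraint is mentioned, and the 2-point margin is absent.

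**The concern.** The stated objective is directional: whether adding Tuina to acupuncture is superior. The sample size follows that question, with one difference, one direction and one margin. The planned primary test does not. A significant interaction says only that the two courses differ somewhere. It can come wholly from week 18, or from effects of opposite sign at the two follow-up visits.

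Because no visit is fixed in advance, the post hoc step lets the data choose which visit carries the claim. If the interaction is not significant, the section provides no test of a treatment difference at any visit. Even a significant visit comparison would be against zero, which is not the hypothesis that produced 60 patients.

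This goes beyond detail an article might leave to an analysis plan. The section states a decision rule, and that rule answers a different question from the one the trial was sized on.

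**Working it through.** **Inputs from the protocol.** Difference 3.25, margin 2, SD 1.5, alpha 0.025, power 0.80, dropout 20%, 30 per group; analysis at two-sided 0.05.

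**Assumptions.** The protocol gives no between-visit correlation, so ρ = 0.3, 0.5 and 0.7 are used, equal between all pairs of visits. SD is 1.5 at every visit, 24 per arm are evaluable, and time is categorical (2 df).

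**1. The protocol's own figure.** The distance beyond the margin is 3.25 − 2 = 1.25.
- Normal approximation: n = 2 × 1.5² × (1.960 + 0.842)² / 1.25² ≈ 22.6, so 23 per arm.
- Noncentral t: power is 0.789 with 23 per arm and 0.807 with 24.
- 24 / 0.8 = 30 per group, which matches. It does so only with 0.025 read as one-sided; two-sided 0.025 would need 29 evaluable per arm.

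So the sized test is one post-treatment comparison against 2 points, with 81% power.

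**2. What the interaction responds to.** Let δ6 and δ18 be the group differences at the two follow-up visits, with none at baseline. The noncentrality is

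λ = n(δ6² − δ6δ18 + δ18²) / [3σ²(1 − ρ)], referred to F(2, 45).

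With δ6 = 0 and δ18 = 1.25: λ = 24 × 1.5625 / [6.75(1 − ρ)] = 5.56 / (1 − ρ), or 7.9, 11.1 and 18.5. Power is 0.68, 0.83 and 0.97. By symmetry the same values apply to an effect present only at week 6, or equal at both visits.

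**3. Power against zero.** The gated route means that the interaction is significant at 0.05 and the raw week-6 group comparison is then significant at 0.05/2 or 0.05/3. Ranges cover ρ from 0.3 to 0.7 and an effect sustained, halved or gone at week 18.

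| True week-6 difference | Gated route | One unadjusted contrast | One baseline-adjusted contrast (ρ 0.3 / 0.5 / 0.7) |
|---|---|---|---|
| 3.25 | near 100% | near 100% | near 100% |
| 2.0 | about 92 to 99% | 99% | above 99% |
| 1.25 | about 44 to 70% | 81% | 84 / 90 / 98% |

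**4. The margin claim at the protocol's inputs.** With a true 3.25 the gate is passed almost surely, so only the alpha split matters. For an unadjusted visit comparison with 1.25 points beyond the margin:
- one-sided 0.025: 81%
- 0.025/2: 71%
- 0.025/3: 66%

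**5. Handling of baseline.** Contrasts taken from the interaction are differences in change from baseline. Relative to a single-visit comparison, their variance is 2(1 − ρ): 1.40, 1.00 and 0.60. With baseline as a covariate it is 1 − ρ²: 0.91, 0.75 and 0.51. Since 1 − ρ² = (1 − ρ)(1 + ρ), the adjusted form is never less efficient. For 1.25 points in a single contrast at 0.05, power is 67 / 81 / 95% for change scores and 84 / 90 / 98% adjusted.

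**The case against.** The strongest reply is that the design is generously powered for what it expects. At the planned 3.25 points the interaction and the gated comparison both have power near 100%, and at 2.0 points the gated route still has at least about 92%. The low figures need a true effect of 1.25 points against zero. In the protocol 1.25 is an excess over a margin, not an expected effect, and it lies below the 2-point difference the protocol itself sets. The correlations are also assumed. At ρ of 0.5 or more with a sustained effect, the interaction alone has at least the power of the sized comparison. All of this stands. A reader might infer that the planned test simply loses much of its power; the documents do not support that without these conditions.

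Two other readings also go too far. A reader might say there is no baseline adjustment, but baseline VAS is in the model as a visit. What is not stated is a covariate or a common baseline mean, and an unseen analysis plan might supply either. A reader might also say that Bonferroni alpha is spent on the baseline visit. The text does not say how many visits are compared, which is why both two and three are shown.

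Finally, the post hoc step would show which visit differs, so a week-18-only effect would not be hidden. That is fair, but it does not settle beforehand which visit decides the trial, and it does not restore the margin.

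**Conclusion.** The point holds as a mismatch between the sized hypothesis and the planned test. It needs correcting before recruitment, which the Results section says is not yet open. The protocol fixes no primary visit, no single primary contrast and no use of the 2-point margin in the analysis. An effect of 1.25 points confined to week 18 would give a significant primary test 68 to 97% of the time.

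The power consequences are secondary and conditional. They are nil at 3.25 points against zero and small at 2.0. At 1.25 points they are material: about 44 to 70% against 81% for one unadjusted contrast. If the 2-point claim is to be made by visit, the alpha split alone takes the planned 81% to 71% or 66%. These figures rest on 24 evaluable per arm, SD 1.5 at each visit and categorical time. The interaction, gated and baseline-adjusted figures also rest on the assumed correlations of 0.3 to 0.7; the 81%, 71% and 66% do not.

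**What to change.** In Statistical Analysis:
- Name one primary visit, for example week 6 as end of treatment.
- Name one primary contrast: the between-group VAS difference at that visit, from the same mixed model, with baseline VAS-by-visit as a covariate or a common baseline mean for both groups.
- Test that contrast directly, without the interaction gate and without a Bonferroni split.
- Make the other follow-up visit a secondary contrast from the same model.
- Use the same form for WOMAC, 10MWT, pain threshold and muscle tension.

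Then reconcile the hypothesis with Sample Size Calculation. Either compare the confidence interval for the primary contrast with the 2-point margin, or restate the sample size as a test against zero. Naming the contrast without doing one of these would leave the sized hypothesis untested. State in both sections which visit the 3.25 points refers to.

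The cost is about a paragraph of wording, with the same data and software. The downside is that the other visit can no longer carry the primary claim.

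### The only missing-data sensitivity analysis is multiple imputation, which as ordinarily run shares the primary model's missing-at-random assumption, so agreement between the two would not show robustness to informative dropout

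*Protocol article*

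**What the plan says.** The Statistical Analysis section of the protocol article says that VAS and the key secondary outcomes "over time will be analyzed using linear mixed-effects models", with a group-by-time interaction across baseline, 6 weeks and 18 weeks, and that the analyses "will adhere to the intention-to-treat principle". On missing data it says: "The mixed-effects models appropriately handle missing data under the assumption that they are missing at random". The next sentence names the one sensitivity analysis: "A sensitivity analysis using multiple imputation will also be conducted to confirm the robustness of the primary results". The article gives no imputation model, no list of auxiliary variables, and no analysis in which the missing values are allowed to differ systematically from what the observed data predict.

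The Sample Size Calculation section sets a superiority margin of 2 VAS points, assumes a difference of 3.25 and an SD of 1.5, and arrives at 30 per group after "accounting for a 20% dropout rate".

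**The concern.** A sensitivity analysis for missing data is useful when it varies the assumption in doubt. Here that assumption is MAR. A likelihood-based mixed model and conventional multiple imputation using the same variables are two routes to nearly the same estimate under that assumption. If it fails, both are biased by about the same amount and still agree, so the agreement would be reported as robustness.

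Several features make outcome-related dropout plausible:

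- Patients know their treatment (Blinding), and the primary VAS is marked by the patient (Primary Outcomes).
- Treatment takes 12 visits in 6 weeks, followed by 12 unsupervised weeks (Interventions; Follow-Up).
- Table 1 schedules post-baseline VAS only at weeks 6 and 18. Someone who leaves during treatment may have no post-baseline score, and MAR prediction then rests on little more than arm and baseline.
- The limitations paragraph accepts that treatment intensity and contact time differ between arms, so reasons for leaving may differ too.

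At stake is how far the estimated benefit of adding Tuina can be trusted, above all against the 2-point margin on which the trial was sized.

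**Working it through.** **Inputs from the article.** Difference 3.25, SD 1.5 per arm, margin 2, alpha 0.025, power 0.80, dropout allowance 20%, 30 per arm (Sample Size Calculation).

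**Assumptions made here, not in the article.** The size of the shift (delta) among leavers; the 20% allowance applied in full at one time point; the standard error left unchanged by the shift; and, in the simulation, the within-patient correlation and the dropout mechanism.

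**Step 1: reproduce the sample size.** The distance beyond the margin is 3.25 − 2 = 1.25. A one-sided t test at 0.025 needs 24 per arm (power 0.807), and 24 / 0.8 = 30. The stated 30 is reproduced and is not affected by this point.

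**Step 2: effect of a shift.** With a fraction 0.20 missing, a shift of delta points among leavers moves the arm mean by 0.20 × delta, that is 0.2, 0.4 or 0.6 for delta = 1, 2 or 3. Write dT and dA for the shifts in the Tuina and acupuncture arms, positive meaning worse pain than MAR predicts. The adjusted difference is

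3.25 − 0.20 × dT + 0.20 × dA.

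Thus dT > 0 alone means MAR overstates the Tuina benefit, dA > 0 alone means MAR understates it, and equal shifts with equal missing fractions cancel.

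**Step 3: set this against zero and against the margin.** With 24 completers per arm, SE = 1.5 × √(2/24) = 0.433 and the critical t on 46 df is 2.013, so the half-width is 2.013 × 0.433 = 0.87. Shifting the Tuina arm only:

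| dT | Adjusted difference | Power against the 2-point margin | Power against zero |
|---|---|---|---|
| 0 | 3.25 | 0.81 | >0.99 |
| 0.5 | 3.15 | 0.74 | >0.99 |
| 1 | 3.05 | 0.66 | >0.99 |
| 2 | 2.85 | 0.48 | >0.99 |
| 3 | 2.65 | 0.31 | >0.99 |

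If the trial observed exactly 3.25, the lower confidence limit would be 3.25 − 0.87 = 2.38. It would reach 2 at dT = 0.38 / 0.20 = 1.9 points. The point estimate itself would reach 2 only at dT = 1.25 / 0.20 = 6.25.

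**Step 4: does MAR imputation reveal the problem?** A simulation used 400 trials, 30 per arm with 6 missing per arm at week 18, SD 1.5, correlation 0.5, true difference 3.25 and 20 imputations. The likelihood estimate under MAR stood in for the mixed model.

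| Mechanism | Complete data | MAR likelihood | MAR multiple imputation |
|---|---|---|---|
| Worst Tuina scores tend to be missing | 3.27 | 3.61 | 3.61 |
| Missing completely at random | 3.25 | 3.25 | 3.25 |

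In the first row the two MAR estimates correlate at 0.997 and differ by 0.03 on average, yet both are about 0.35 too large (3.61 − 3.27 = 0.34 from the rounded figures). Their agreement is just as close in the second row, where there is no bias. It therefore carries no information about whether MAR holds.

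**The case against.** The strongest objection is that the article ties MAR to the mixed model only. Delta-adjusted and reference-based methods are also multiple imputation, and an analysis plan that is not shown could specify them. That is correct, and a reader who inferred that the article commits its imputation to MAR would go beyond the text. But the article does more than leave detail open. It gives unqualified multiple imputation the job of confirming robustness, directly after a sentence on MAR, and no departure from MAR appears anywhere.

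Imputation can also bring in auxiliary variables and so make MAR more credible. This stands in part: it gives a somewhat different MAR model, but not a departure from MAR. WOMAC is scheduled at the same visits as VAS in Table 1, so a patient who misses a visit would usually lose both.

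Three further inferences are tempting and not supported:

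- *The bias favours Tuina.* Disappointment with allocation fits the acupuncture-only arm at least as well, and there it would hide benefit.
- *The comparison with zero is in danger.* At the planned effect, shifts of 0.2 to 0.6 do not threaten it.
- *A better analysis would detect informative dropout.* No analysis of observed data can. Delta adjustment shows how strong it would have to be to change the conclusion.

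Finally, 20% is a sample-size allowance and not a forecast, and the mixed model keeps week-6 data from patients lost later. The figures above are illustrations for that reason.

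**Conclusion.** The concern holds in a limited form. As worded, the plan's single check would not show robustness to informative dropout, because imputation as ordinarily run keeps the assumption in doubt. The consequence depends on the criterion. Under the planning values (difference 3.25, SD 1.5, 24 completers per arm) a test against zero is secure. A claim of exceeding the 2-point margin is not: power drops from about 0.81 to about 0.66 or 0.48 if Tuina-arm leavers are 1 or 2 points worse than predicted. A true effect smaller than the preliminary 3.25 would leave less room on either criterion. The shifts are assumed, the direction depends on which arm loses the worse patients, and neither the sample size nor the primary model is called into question.

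**What to change.** Keep the MAR imputation if wanted, but do not describe it alone as confirming robustness. Add a prespecified delta-adjusted multiple imputation of VAS:

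- Add delta to the imputed values over a stated grid, for example 0.5 to 3 points in steps, extended if needed to reach the tipping point.
- Vary delta independently by arm: Tuina only, acupuncture only, and both.
- Report the tipping point against the trial's success criterion, and say whether that criterion is zero or the 2-point margin.
- Optionally, add a reference-based run that imputes Tuina dropouts from the acupuncture arm.

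The cost is a short additional program in R, which the plan already uses, and some extra reporting. The primary analysis does not change. The article says recruitment is not yet open and that analysis starts after the last follow-up, so the grid can be fixed before any outcome is seen. Deltas chosen afterwards would carry much less weight.

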**Methods:**

This single-center, parallel-group, randomized controlled trial aims to enroll 60 patients with KOA, who will be randomly assigned to either a Tuina group (acupuncture-combined Tuina) or an acupuncture group (30 patients per group). Baseline assessments will include demographic and clinical evaluations: the visual analog scale from the short-form McGill Pain Questionnaire, pain threshold, muscle tension, 10-meter walking test, Western Ontario and McMaster Universities Osteoarthritis Index, and multimodal magnetic resonance imaging. Over a 6-week intervention, the Tuina group will receive Tuina on the basis of acupuncture, that is, acupuncture-combined Tuina, while the acupuncture group will undergo just acupuncture, with both groups continuing standard care as prescribed. Posttreatment, clinical outcomes and safety will be reassessed using baseline indicators. A 12-week follow-up will include all clinical evaluations. Assessments will be conducted by blinded assessors, and statistical analyses will be conducted by independent, blinded analysts. Outcomes will evaluate clinical pain and functional differences between groups and will elucidate the underlying cerebral mechanisms.

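### Correlations between outcome changes carry no term for treatment arm; if the arms are pooled and treatment shifts both outcomes, unrelated changes can correlate

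*Protocol article*

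**What the plan says.** The protocol article's Statistical Analysis section fits linear mixed models with a group-by-time interaction to VAS, WOMAC, the walking test, pain threshold and muscle tension. A two-sided P value below .05 is "considered statistically significant". A single sentence then covers relations among outcomes: "Correlations between changes in different outcomes will be assessed using Pearson or Spearman coefficients". It names no outcome pairs, no covariate and no stratification, and does not say whether a coefficient uses all patients or one arm.

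No other section adds this. Analysis of Multi-MRI Data describes image processing and group comparisons but no method for relating imaging change to clinical change. The Abstract says the outcomes "will elucidate the underlying cerebral mechanisms". Study Strengths and Limitations describes the imaging evidence as preliminary and hypothesis-generating.

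Sample Size Calculation supplies the only effect size in the article. It says that "the mean difference between the acupuncture group and the Tuina group (acupuncture-combined Tuina) is 3.25", "with an SD of 1.5 in both groups".

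**The concern.** A Pearson or Spearman coefficient over both arms mixes two things: how the changes go together among patients treated alike, and how far apart the arm means lie. If treatment moves both outcomes, the second part alone produces a correlation, even when patients who improve more on one measure within an arm improve no more on the other.

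The trial is planned on a large between-arm VAS effect, and the mixed models look for arm effects on four further outcomes. Arm as a common cause of both changes is therefore close to the planned scenario. A pooled coefficient might then only restate that treatment affected each measure, yet be taken as information about how patients' changes relate. Even for hypothesis-generating work, that would point later studies at the wrong pairs.

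**Working it through.** **Inputs from the article (Sample Size Calculation).** Between-arm VAS difference 3.25; SD 1.5 per arm; margin 2; α .025; power 0.8; dropout 20%; 30 per arm, allocated 1:1.

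**Assumptions, not in the article.** The effect d2 on the second outcome, in SD units; zero within-arm correlation; normal data; and 1.5 as the SD of VAS change as well as of the score. With equal SDs at both visits, SD(change) = 1.5 × √(2(1 − ρ)), which equals 1.5 only if the baseline-to-follow-up correlation ρ is 0.5. A lower ρ makes the standardised effect smaller, a higher one larger.

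**Step 1: the plan's own figure.** The article states no figure for the correlations, so the check is on the sample size. The margin statement is "a 2-point difference on the visual analog scale (VAS) score was defined as the superiority margin", so the effective difference is 3.25 − 2 = 1.25. With one-sided α 0.025:

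n = 2 × (1.96 + 0.84)² × 1.5² / 1.25² ≈ 22.6, so 23 per arm; 23/0.8 = 28.75, so 29.

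The noncentral t calculation gives 24 per arm (power 0.807), and 24/0.8 = 30. The stated 30 per arm reproduces. After 20% dropout, 60 × 0.8 = 48 patients remain, so N = 48 and N = 60 bracket the analysis.

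**Step 2: correlation produced by arm alone.** With 1:1 allocation and zero within-arm correlation,

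r = (d1·d2/4) / √[(1 + d1²/4)(1 + d2²/4)].

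For VAS, d1 = 3.25/1.5 = 2.17 and 1 + d1²/4 = 2.174. For d2 = 0.5: r = 0.271 / √(2.174 × 1.0625) = 0.271/1.520 = 0.178.

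**Step 3: false-positive rate.** Simulation, 10,000 trials per case, two-sided 5% test of the pooled Pearson coefficient:

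| d1 (VAS) | d2 (assumed) | pooled r | N = 48 | N = 60 |
|---|---|---|---|---|
| 2.17 | 0 | 0.00 | 5% | 5% |
| 2.17 | 0.3 | 0.11 | 11% | 14% |
| 2.17 | 0.5 | 0.18 | 23% | 28% |
| 2.17 | 0.8 | 0.27 | 49% | 59% |
| 2.17 | 1.0 | 0.33 | 67% | 77% |
| 1.33 | 0.5 | 0.13 | 15% | 17% |
| 1.33 | 1.0 | 0.25 | 42% | 49% |
| 0.5 | 0.5 | 0.06 | 7% | 7% |

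The rows at 1.33 take a true VAS difference equal to the 2-point margin (2/1.5). Spearman gives nearly the same rates. The sign of r depends on how each change is coded; the size does not.

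**Step 4: after adjustment.** Centring each outcome on its arm mean (a partial correlation given arm, tested on N − 3 rather than N − 2 degrees of freedom) gives a mean r of about 0 and a rate of 4.5% to 5.4% in every case.

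**The case against.** The strongest reply is that pooling is nowhere stated. The sentence speaks of coefficients in the plural, and Pearson or Spearman coefficients computed separately in each arm fit it fully and have none of this bias. A condensed article may leave that choice to an analysis plan that is not shown. This stands in part: the bias is conditional. What remains is that the only method named has no place for arm, no other section supplies one, and the sentence as written allows the version that misleads.

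A reader might also infer that the plan will present a spurious mechanistic link between brain change and pain relief. The article does not support that. The correlation sentence mentions neither imaging nor mechanism, the imaging analysis section mentions no such correlation, and nothing says how a coefficient will be interpreted. Use for imaging-clinical pairs is plausible given the stated aim, but it is inference. The point applies equally to purely clinical pairs.

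Third, the size depends on effects that the article does not give. With modest effects on both outcomes the inflation is slight, and with no effect on the second there is none. Zero within-arm correlation is also unlikely for close relatives such as VAS and WOMAC pain. The pooled value is then still not the within-arm one: with a within-arm correlation of 0.3 and d2 = 0.5, the pooled r is (0.3 + 0.271)/1.520 = 0.38.

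**Conclusion.** The point holds conditionally. If the arms are pooled without adjustment and treatment shifts both outcomes, correlations between changes will partly or wholly reflect arm. Taking the planning VAS effect as the effect on change, and zero within-arm correlation, an assumed second-outcome effect of 0.5 to 1.0 SD yields significant results in about 23% to 77% of trials where 5% is intended. The inflation falls to about 7% when both effects are 0.5 SD.

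The article should not be read as stating that the arms are pooled or that these coefficients will serve as proof of mechanism; it says neither. The analysis is exploratory, and neither the primary comparison nor the sample size depends on it. It still merits correction: a better method is available at almost no cost, and the article reports that recruitment had not opened.

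**What to change.** In Statistical Analysis, replace the correlation sentence with:

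> Associations between changes in outcomes will be estimated by partial correlation (Pearson or rank) adjusted for treatment arm, with within-arm coefficients also shown.

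If within-arm coefficients were always intended, saying so resolves the point. Adjustment for baseline values is optional; removing the arm effect is enough to restore the nominal rate in Step 4. The cost is one sentence and one degree of freedom per coefficient, with no new data.
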